#### First Assay

Epigenetic marks will be assessed with blood tests. The samples will be collected by qualified and verified professionals, from veins located in the antecubital area, in a sanitized and cool place previously prepared for the procedure. Furthermore, 20 mL blood will be drawn using disposable syringes and needles. The venipuncture procedure will be applied and all national biosafety procedures will be followed. Initially, the blood will be divided into two tubes: a tube containing a separating gel that will receive 5 mL blood to obtain the serum. The other tube will contain the EDTA anticoagulant and will receive 15 mL blood. Then, Histopaque will be added in a 1:1 ratio to the tube with EDTA, which will then undergo a series of centrifuges for the extraction of plasma and peripheral blood mononuclear cells. The material will be stored in appropriate containers at −20 °C. Biomarker analysis will be performed using commercially available assay kits, according to the manufacturer’s guidelines.

The types of indicators that will be analyzed using biomarkers include plasma levels of the brain-derived neurotrophic factor (BDNF), a member of the neurotrophin family that has an important role in neuroplasticity and is associated with the process of memory and learning. We will also analyze the global acetylation levels of histones H3 and H4, which are epigenetic markers associated with increased transcriptional activity and gene expression. A previous study [9] identified that a single exercise session induced a state of global DNA hypomethylation but did not alter the global acetylation levels of H4 histone. However, these markers were not modified after more sessions, suggesting that epigenetic modulation in response to physical exercise is transient, which justifies an analysis comparing the acute and late effects.

Cognitive ability will be assessed using the Brazilian version of the Montreal Cognitive Assessment protocol [38]. This is a brief screening tool that assesses a wide range of cognitive functions, such as executive functions, visuospatial skills, memory recovery, digits, sentences, abstract reasoning, and orientation. The test time is estimated at 20 minutes and the maximum possible score is 30 points. The cutoff score is 26 points.

#### Second Assay

The balance will be assessed using the Timed Up and Go test, which determines fall risk and measures, in seconds, the time taken by an individual to stand up from a chair, walk a distance of 3 m, turn, walk back to the chair, and sit down. For healthy older adults, the ideal time for the test is 10 seconds. When performed between 11 and 20 seconds, it indicates that the individual may have some disability or fragility, which is considered partial independence and low risk of falls. When the test is performed with a time ≥20 seconds, the individual is classified as dependent and has a considerable deficit in physical mobility and a high fall risk [39,40].

Muscle strength grading will be assessed using a push-pull hydraulic dynamometer. This is a device that operates on the principle of traction and compression. An external force is applied to the dynamometer and its spring is tensioned, moving an indicator of the amount of static force applied.

Game experience will be assessed using the postgame module of the Game Experience Questionnaire [41]. It measures players’ experience after the gaming session and any aftereffects (eg, returning to reality, fatigue, pride, guilt) using 17 statements with a semantic differential scale response to indicate the level of agreement.

### Procedure and Follow-up

During the study, participants in both groups will not be allowed to perform any other type of physical therapy. Intervention sessions for both groups will be carried out twice a week. Each session will last an hour, for 6 weeks, resulting in 12 sessions. This time frame is based on similar studies of Duque et al [42] and Park and Yim [43]. The set of kinesiotherapy exercises was designed based on exercises from successful studies on older rehabilitation [21,44,45], whose movements can be captured by the motion sensor used in the exergame.

We will request all participants to attend sessions wearing dark workout clothes to standardize them and also facilitate body detection by the motion sensor. Each participant will be placed in a room with the setup ready. For the control group, it will be a conventional physiotherapy clinic with the necessary equipment for the exercises. For the intervention group, the environment will contain the same equipment, along with the exergame setup consisting of a 42-inch monitor and the motion sensor.

Both groups will be accompanied by 2 physical therapists throughout the sessions. The professionals will provide instructions and adjust the equipment used in the sessions following a standardized procedure protocol to avoid any type of bias. In the event of an incident (eg, harmful movement, injury, or misuse of equipment), the professional will intervene, pausing the session until the problem is fixed. The session will resume as soon as possible so that the participant can complete the remaining time.

The exercises will use dumbbells, TheraBands, and Swiss ball accessories. The weight of the dumbbells and resistance level of the TheraBand will be proportionally tailored to each participant. We will use the Modified Borg Dyspnea Scale [46] to verify the participant’s perception of effort and to define the accessories with an inversely proportional level of difficulty of use. In the first intervention session, for all participants, we will provide a 1-kg dumbbell and a light-resistance TheraBand. Then, at the end of each session, the physical therapists will evaluate each participant’s perception of effort in performing the exercises using her respective accessories. This will support the choice of the dumbbell weight and the TheraBand resistance that the participant will use in the following session. Different Swiss balls will be used, depending on the height of the participant: the small version of 55 cm for people with a height of 160–174 cm, and the average version of 65 cm for people with a height of 175–195 cm.

Performed individually, the kinesiotherapy session will start with a warm-up exercise (10 minutes), using a horizontal exercise bike. After that, the following 8 specific exercises will be performed:

Squatting with dumbbells in hands, for 3 minutes.Horizontal shoulder abduction with elbows in extension holding the TheraBand and sitting on the Swiss ball, for 3 minutes.Hip abduction with the TheraBand around the lower limbs, for 6 minutes.Kabat diagonals (adapted) with the patient sitting on the Swiss ball, for 6 minutes.Plantar flexion for calf with dumbbells in hands, for 3 minutes.Horizontal shoulder adduction with elbows in extension holding the TheraBand and sitting on the Swiss ball, for 3 minutes.Elbow flexion for biceps using TheraBand and sitting on the Swiss ball, for 3 minutes.Flexion of hamstring, quadriceps, iliopsoas, and gastrocnemius, performed during a series of 30 seconds for each muscle group, repeatedly, for 6 minutes.

After the strength exercises, the participants will perform cervical spine stretching, lateral and posterior trunk stretching, hamstring stretching, and quadriceps, iliopsoas, and gastrocnemius exercises. The exercises will be performed in a series of 30 seconds, resulting in 10 minutes of activities. Among the different types of exercises, there will be intervals of at least 30 seconds for rest and adjustment of game settings.

The intervention group will perform the same procedure and use the same kinesiotherapy equipment as the control group but playing the exergame with its 8 specific exercises as the basis of the session. The exercises will always be performed in the same order and duration, from the first to the last session. During the intervention, there will be a tolerance of only 2 absences per participant, which must be recovered immediately in the same week of the absence. Otherwise, the participant will be removed from the study.

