### Sample, Eligibility, and Allocation

We will recruit 24 participants, exclusively women aged 60 years and over, at the School Clinic of Studies and Professional Practices of the Regional Integrated University of Upper Uruguay and Missions, which is located in Erechim, Rio Grande do Sul, Brazil. The sample size was based on the studies that used a similar methodology to assess the effect of exercise on epigenetic marks and the effect of improved functional mobility induced by running in the older women, related to epigenetic marks [8,9], considering the global H4 histone acetylation levels variable from earlier studies [33,34]. Sample size was calculated using G*Power software [35] considering an effect size of 1.3, two tails, an error probability of .05, and a power of 0.8.

After the invitation to take part in the study, the participants will sign a consent form and complete a demographic questionnaire. The following inclusion criteria will be verified: age 60 years or older; ability to ambulate effectively; absence of any reported diagnosis of neurological, cardiac, or any other disease that restricts physical exercise; absence of depression confirmed by the Geriatric Depression Scale—Short Form [36]; cognitive ability confirmed by the Mini-Mental State Examination, Brazilian version [37]; and acceptance of the commitment not to undergo any other physical therapy during the study.

The sample will have stratified randomization for 2 groups with 12 participants each. Patients will be selected by order of agreement to participate in the study until the number of patients stipulated for either of the groups is reached. The intervention group will practice kinesiotherapy exercises with the exergame, whereas the control group will practice conventional kinesiotherapy exercises without exergaming. Owing to the nature of the intervention, masking of the physical therapists and participants is not possible. However, data will be collected and analyzed by professionals masked to the allocation of the groups.

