### Outcome Measurements

Throughout the clinical trial, we will assess different data for two assays. The first assay will assess the acute and late effects on the participants’ epigenetic marks (primary outcome) as well as the cognitive ability (secondary outcome). Meanwhile, the second assay will assess the participants’ balance and muscle strength grading (primary outcomes), in addition to the postgame experience (secondary outcome).

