### Data Collection

Blood test values to assess epigenetic marks will be collected from all participants at three stages: at baseline; after the first session of the intervention, to verify the acute effects; and after the complete intervention, to verify the late effects. Cognitive ability, balance, and muscle strength values will also be collected from all participants at two stages: at baseline and after the complete intervention. Game experience data will be collected exclusively from the participants who played the game (intervention group) after the intervention is completed.

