We expect that both groups have improvements in muscle strength, balance, and cognitive ability, as both of them will exercise. However, due to the motivational and enriching aspects of the exergame, we expect the intervention group to show a significant improvement compared to the control group. We assume that improvement in functional clinical outcomes in the exergame group will be associated with increased BDNF levels and global acetylation of histones H3 and H4. Strategies that modulate BDNF and acetylation levels might be indicated to improve memory in the older population. Many studies have already shown that exercise is a strong epigenetic modulator that increases BDNF levels [7-9,33,62].

Research on this topic is likely to significantly expand the understanding of kinesiotherapy and the impact of exergames for older women. To the best of our knowledge, this may be one of the first studies exploring epigenetic outcomes of exergaming interventions.

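### The co-intervention rule covers only other physical therapy, so recent or outside exercise is neither limited nor recorded and can blur the within-person acute and late marker changes

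*Protocol article*

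**What the plan says.** The rule on co-interventions appears twice in the Protocol article. Under Procedure and Follow-up: "During the study, participants in both groups will not be allowed to perform any other type of physical therapy". Among the inclusion criteria in Sample, Eligibility, and Allocation: "acceptance of the commitment not to undergo any other physical therapy during the study". Both name physical therapy only, and both apply only while the study runs.

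One other entry criterion mentions exercise: "absence of any reported diagnosis of neurological, cardiac, or any other disease that restricts physical exercise". It screens out women who cannot exercise and says nothing about how much the others already do.

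Blood is drawn three times, "at baseline; after the first session of the intervention, to verify the acute effects; and after the complete intervention, to verify the late effects". Outcome Measurements makes the acute and late effects on epigenetic marks the primary outcome of the first assay. First Assay lists the blood indicators: plasma BDNF and global acetylation of histones H3 and H4. No section limits or records exercise outside the trial or sets a condition on recent exertion before a draw.

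**The concern.** The rule is narrower than the article's own reasoning requires. The Discussion treats exercise in general, not only physical therapy, as acting on the markers: "exercise is a strong epigenetic modulator that increases BDNF levels". First Assay justifies comparing acute with late effects by earlier findings "suggesting that epigenetic modulation in response to physical exercise is transient". If the response is short-lived, what a woman did shortly before a draw matters to that draw, and the baseline draw is the reference for both effects.

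Under the rule as written, a woman may attend a gym or dance class throughout, take one up in week 3, or exercise on the morning of her baseline draw, and still be fully compliant. Nothing in the described data collection would reveal it. At stake is whether a change from baseline can be attributed to the trial sessions. A secondary loss is noise in a comparison of 12 against 12.

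**Working it through.** **1. The plan's own figure.** Inputs from Sample, Eligibility, and Allocation: effect size 1.3, two-sided error probability 0.05, power 0.80, 24 women in two arms of 12. The article does not name the test. A two-sample t-test (noncentral t) needs 10.34, so 11 per arm and 22 in total. Dividing by the minimum asymptotic relative efficiency of the Mann-Whitney test, 10.34 / 0.864 = 11.97, gives 12 per arm and exactly 24. The stated size reproduces. Power of the t-test at 12 per arm is 0.861.

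**2. Where outside exercise enters.** Let X be 1 if a marker shift s from non-trial exercise is present at a draw and 0 if not, and let τ be the true effect of the trial sessions. The change from baseline to draw k is then

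change = τ + s × (X at draw k − X at baseline).

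- Steady outside exercise (X equal at both draws): the change is τ and the shift cancels.
- Exercise shortly before baseline only: the change is τ − s, understated if s is positive, as the Discussion supposes for BDNF.
- Exercise begun during the study, or shortly before the later draw only: the change is τ + s, overstated.

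The within-person change is therefore distorted only when outside exercise differs between draws.

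**3. The contrast between arms.** The difference in mean change equals the true difference plus s times the between-arm difference in the mean of (X at draw k − X at baseline). Habits formed before allocation have the same expectation in both arms, so they add no systematic bias. Activity that changes after allocation has no such protection, because women and therapists know the arm.

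**4. Illustrative size.** The document gives no size for the influence of outside exercise, so these ranges are assumptions. If it adds a fraction v to the outcome variance, the effect size becomes 1.3 / √(1 + v):

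| v | effect size | power at 12 per arm | n per arm for 80% |
|---|---|---|---|
| 0 | 1.30 | 0.86 | 11 |
| 0.10 | 1.24 | 0.83 | 12 |
| 0.25 | 1.16 | 0.78 | 13 |
| 0.50 | 1.06 | 0.70 | 15 |
| 1.00 | 0.92 | 0.58 | 20 |

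To judge v: if a proportion q of women carry a shift of s SD at the draw analysed, v = q(1 − q)s². This is largest at q = 0.5, so v = 0.25 needs at least a 1 SD shift in half the women, and v = 1.00 at least 2 SD. The smaller rows are the more plausible ones.

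If activity after allocation narrowed the contrast to 90% or 80% of 1.3, power would be 0.78 or 0.68.

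**The case against.** Much of the opposing case stands.

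- **H4 acetylation.** First Assay reports that "a single exercise session induced a state of global DNA hypomethylation but did not alter the global acetylation levels of H4 histone". H4 acetylation underlies the sample size, and DNA methylation, the mark that did change, is not among the listed indicators. Acute carry-over into H4 is therefore not shown. The support is for BDNF, with only the Discussion's general expectation for H3 and H4.
- **Washout.** A reader might infer that women should be free of exercise programmes for weeks before baseline. The document does not support this: a transient response argues against long carry-over, and First Assay says the markers were not modified after further sessions. At most, a condition close to each draw is supported. Recruitment at a university clinic might also suggest that women arrive from another programme, but no section says so, and the interval from consent to the baseline draw is not given.
- **Chance imbalance.** If 20%, 30% or 50% of women exercised outside the trial (assumed), two arms of 12 would differ by 3 or more exercisers with probability 0.20, 0.26 or 0.31. A reader might call that bias. It is sampling variation, already within the standard error of √(2/12) = 0.41 SD.
- **Differential activity after allocation.** This is possible but not documented. Controls receive the same exercises for the same time.
- **Condensed article.** Pre-draw conditions often sit in a fuller protocol or a sampling procedure, so their absence alone would be no finding. That does not rescue the co-intervention rule, which the article states in two places and with a scope too narrow for its own rationale.

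**Conclusion.** The concern holds in a limited form. The stated rule leaves recent and outside exercise compatible with the protocol, and the plan does not record it. The consequences are blurred within-person acute and late changes (chiefly BDNF), added variance at 12 per arm, and a possible difference between arms in activity after open allocation. The documents do not support the stronger reading that the randomised comparison is systematically biased by women's existing habits, nor any figure for such a bias.

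The size is unknown. The power figures rest on assumed variance inflation or dilution, on an additive shift, and on a t-test at effect size 1.3. The SD behind that effect size may already include some outside exercise, in which case the loss is smaller. This is a worthwhile and inexpensive improvement to a primary outcome, not a threat to the trial's validity.

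**What to change.** 1. In Sample, Eligibility, and Allocation and in Procedure and Follow-up, extend the commitment so that, besides other physical therapy, women agree not to start or change any other structured exercise programme or exergame during the study. Women with a steady habit can still take part.
2. In Data Collection, add for each blood draw a condition of no deliberate exercise shortly beforehand other than the trial session itself, with the interval set by the sponsor. Confirm it with one recorded question, and reschedule the baseline draw if the condition is not met.
3. Record outside exercise at each draw, so that imbalance between arms, or change over time, can be seen and examined in a sensitivity analysis.

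The cost is a wording change in three sections, one extra question per draw and a few rescheduled baseline visits.

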### Exergame Development

Exergames that require an individual to repeatedly reach for an object do not use the full potential of exergaming as a rehabilitation tool [31]. Taking this into account, we will develop an exergame with a virtual scenario based on a physiotherapy clinic. In this environment, 8 types of exercises practiced in kinesiotherapy sessions will be available, including squats, horizontal shoulder abduction, hip abduction, diagonal movement of the upper limb (Kabat diagonals), plantar flexion, elbow extension, elbow flexion, and horizontal shoulder adduction. Reference images from real environments will be used to model the setup and all interactable objects used by the avatars.

The clinic scenario will have windows that show an outdoor view with trees and clouds reacting to the wind. The lighting and animations will also change according to the day and time the user is playing, whether day or night. A male and a female character (avatar) will be available to play, selected according to the gender registered for each user. The objects that the avatar will interact with when performing an exercise will be automatically selected according to the type of exercise. Four camera positions will be implemented in the game. The game will have a menu with options for registration, settings, and types of exercise. During the execution of the exercises, information on the number of repetitions and completed series will appear on the screen, in addition to the execution time.

The exergame will be developed using the programming language C# (Microsoft Corporation), with the game engine Unity 3D (Unity Technologies). Both the scenario and the physiotherapy equipment will be modeled on Blender (Blender Foundation), open-source 3D creation software for animation, simulation, rendering, composition, and motion tracking. The characters will be created in Adobe Fuse (Mixamo), which also offers prebuilt animations and an autorigging tool in the mesh of the created characters. Some other tools, such as Audacity, for editing the sound effects, and Paint.NET (dotPDN LLC) for editing the interface sprites and object textures, may be used in the development of the game.

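### The game's 8 exercises and the session's 8 exercises differ by one item, so it is unclear whether both arms do the same exercises

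*Protocol article*

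**What the plan says.** Three statements in the protocol article bear on this.

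- **Exergame Development** describes the software: "8 types of exercises practiced in kinesiotherapy sessions will be available". The list that follows is complete at 8 and ends with "plantar flexion, elbow extension, elbow flexion, and horizontal shoulder adduction". It gives no durations.
- **Procedure and Follow-up** describes the session. After the warm-up, "the following 8 specific exercises will be performed", again with a complete list of 8, each with a duration. Its only elbow exercise is "Elbow flexion for biceps using TheraBand and sitting on the Swiss ball, for 3 minutes". Its last item, which takes 6 minutes in all, is "Flexion of hamstring, quadriceps, iliopsoas, and gastrocnemius, performed during a series of 30 seconds for each muscle group".
- **Procedure and Follow-up**, a little further on, links the two. What the intervention group does is described as the "same procedure and use the same kinesiotherapy equipment as the control group but playing the exergame with its 8 specific exercises". Sessions in that arm are thus to be built on the game's exercises. The order and duration of the exercises are fixed for all sessions.

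The same section says that the chosen exercises have movements that the game's sensor can capture.

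**The concern.** The game is the only intended difference between the arms. The Discussion expects the intervention arm to do better because the game motivates and enriches, which presupposes equal exercise content. The linking sentence is the one place that secures this equality, and it leans on two lists that do not agree. In that sentence the possessive points to the exergame, and so to the game list, while the phrase about 8 specific exercises is the one used to introduce the session list.

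At stake is what a difference between arms would mean. Muscle strength and balance (Timed Up and Go) are the primary outcomes of the second assay. If one arm trained the lower limbs for longer and the other trained elbow extension, that difference would coincide exactly with the allocation. No analysis could then separate it from the effect of the game.

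**Working it through.** **Step 1. Set the lists side by side** (inputs: Exergame Development; Procedure and Follow-up).

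| Exercise | Game list | Session list (minutes) |
|---|---|---|
| Squat | yes | 3 |
| Shoulder abduction, horizontal | yes | 3 |
| Hip abduction | yes | 6 |
| Kabat diagonals | yes | 6 |
| Plantar flexion | yes | 3 |
| Shoulder adduction, horizontal | yes | 3 |
| Elbow flexion | yes | 3 |
| Elbow extension | yes, no duration | absent |
| Lower-limb flexion series | absent | 6 |

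Each list has 8 items, as stated. Seven are shared, and each list has one item that the other lacks. The session's two shoulder exercises are done with the elbows extended. That is an arm position, not an elbow-extension exercise, so it does not supply the missing match.

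**Step 2. Size of the unmatched session item.**

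- Specific exercises: 3 + 3 + 6 + 6 + 3 + 3 + 3 + 6 = 33 minutes.
- Share of the lower-limb series: 6 / 33 = 18%.
- Over the course: 6 × 12 sessions = 72 minutes.

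The share of elbow extension cannot be computed, because no duration is given.

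**Step 3. Is the session list consistent with the stated hour?** Warm-up 10 + exercises 33 + stretching 10 = 53 minutes. Depending on how the rests are counted, 7 to 9 rests of 0.5 minutes add 3.5 to 4.5 minutes, giving 56.5 to 57.5 minutes. The session list fits the hour, so the timing reveals no error in it.

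**Step 4. What the linking sentence implies under each reading.**

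| Reading | Exercise content | Game coverage |
|---|---|---|
| A. The intervention arm performs the game list | Differs: lower-limb series (6 minutes per session) in control only, elbow extension in intervention only | 8 of 8 game exercises used |
| B. Both arms perform the session list, with the lower-limb series off-screen in the intervention arm | Same | 7 of 8 session exercises; 33 − 6 = 27 of 33 minutes (82%) |
| C. One list is a drafting slip | Same | 8 of 8 |

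Reading A breaks the same-procedure half of the sentence. Reading B breaks the half that makes the game's 8 exercises the basis of the session, and it sits awkwardly with the statement on sensor capture. Reading C contradicts nothing once corrected, but the text does not show which list would be the slip.

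**The case against.** The strongest defence is that the session list is meant for both arms. The linking sentence says outright that procedure and equipment are the same. The session description includes rests used partly to adjust game settings, which concerns only the game arm. Only the session list carries durations, so the fixed order and duration most naturally refer to it. The game list says what the software makes available, and availability is not prescription. A standardised procedure protocol is also mentioned, and it may hold the detail that an article condenses. On this view, the software description is simply out of step.

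Much of this stands, and it rules out two stronger claims:

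- A reader might infer that the arms cannot follow the same procedure, or that the comparison does mix game and content. The document does not show that. Readings B and C leave exercise content equal.
- A reader might infer that elbow extension, as a ninth exercise, would overrun the hour. No passage proposes a ninth exercise or gives it a duration. If 3 minutes plus one rest is assumed, the total is 56.5 + 3.5 = 60 or 57.5 + 3.5 = 61 minutes, depending on how rests are counted. This settles nothing.

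It is also fair to say that Outcome Measurements does not name the muscle groups tested with the dynamometer. How far one exercise would shift measured strength is therefore unknown, and nothing in the document supports a claim about its effect on the biomarkers.

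The defence does not remove the conflict itself. This is not a detail lost in condensation: two complete lists, each said to number 8, disagree, and the sentence defining the intervention relies on both.

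**Conclusion.** The point holds as a contradiction in the definition of the intervention. The lists differ by 1 item of 8, and the linking sentence cannot be met in full as written, so it is unclear whether both arms do the same exercises.

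The consequence is conditional. Under reading A, control alone would receive a lower-limb series worth 6 of 33 exercise minutes (18%) per session, and the intervention arm alone would receive elbow extension of unstated length. The effect of the game on strength and balance would then be confounded with content. Under reading B, the comparison of content is sound, but the intervention is a game covering 7 of the 8 session exercises. The size of any bias under reading A cannot be estimated from the document.

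The conclusion rests on taking both lists as complete, which their stated count of 8 supports. The sample size is not affected. Because the inconsistency sits in the only intended contrast between arms, and delivered sessions cannot be corrected afterwards, it should be resolved before the first session.

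**What to change.** Reconcile the exercise list in Exergame Development with the session list and the linking sentence in Procedure and Follow-up. The result should be one exercise list, with one duration per exercise, that applies to both arms and matches what the software delivers. Add a sentence saying that any item done without the game in the intervention arm is done identically in control, and name such items. Which exercise is kept, and for how long, is for the clinical team.

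The cost is protocol wording and possibly enabling or disabling one exercise in the game. The Results section places game development in 2020 and still describes recruitment as planned, so on the document's own timeline the change can be made before any participant is treated.
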